## 2. Methods

### 2.1. Design

This study is a parallel, three-group, randomized, controlled trial investigating the effects of printed computer-tailored lifestyle intervention (LI) on favorable lifestyle change, and the effects of genetic counseling (GC) about prevention and hereditary risk of type 2 diabetes on the compliance to the life style intervention.

Data collected at preintervention, immediately post-GC (baseline), and at 1 week and 3, 6, and 12 months post-GC will be analyzed. The design, conduct, and reporting of the study adhere to the Consolidated Standards of Reporting Trials (CONSORT) guidelines [47].

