#### 2.3.1. Genetic Counseling

After written consent was obtained, subjects underwent genetic counseling with a certified genetic counselor. The counseling session used the booklet developed by the authors, which has been described elsewhere [48]. Briefly, the booklet consists of four sections, each reflecting a core element of the health belief model, with the following information provided in each section. (1) *Perceived seriousness.* Information on the symptoms and complications of diabetes. (2) *Perceived susceptibility.* Information on the drastic increase in the number of diabetic patients, and the implications of genetic-environmental interactions. Causes of diabetes, such as genetic predisposition, high-fat foods, and/or a sedentary lifestyle [11, 49]. Information on genetic predisposition, decreased insulin secretion, and the decreased insulin sensitivity caused by a high-fat meal [21]. Advice that individuals with an affected first-degree relative have a 2.3–5.5-fold higher risk of developing type 2 diabetes [19] since such individuals seem to have similar genetic predisposition and lifestyle. (3) *Perceived benefits.* Advice that the risk of acquiring diabetes can be modified by a low-fat diet and increased physical activity (PA) [50, 51]. (4) *Perceived barriers.* A summary of concrete methods to modify diet and PA, and a recommendation to refer to professionals for individualized prevention [50, 51]. The total time for the counseling session was approximately 10 min.

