(2) Generation of Tailored RecommendationsLISS-DP will be used to assess each subject's lifestyle behaviors and generate individualized recommendations according to the following algorithms (Figure 2). First, subjects will be divided into four groups according to their combination of risk factors, sex, and physical activity level: male/high-PA group (A), male/low-PA group (B), female/high-PA group (C), and female/low-PA group (D). A high physical activity level is defined according to the national health promotion policy (Healthy Japan 21) as ≥30 min of moderate physical activity ≥2 days/week. LISS-DP will then select the items to be assessed in each risk group. In addition to these selected items, subjects with obesity-related risk factors, high BMI, and/or large waist circumference will be assessed using items which have a relationship with obesity. Cut-off point for each obesity-related risk factor was set based on those of national screening program (SHC, mentioned previously). If subjects answer “never” or “rarely” to one of the selected RD or RP items, that item will be identified as a behavior which the subject should aim for. If subjects answer “often” or “always” to one of the selected ND, that item will be identified as a behavior which the subject should refrain from. If subjects answer “always” to NP item, it will be also identified as a behavior which the subject should refrain from. Additionally, if subjects answer “often” or “always” to one of the RD or RP items, that item will be identified as a behavior which should be continued.

(3) Output of Tailored RecommendationsDietary and PA behaviors which should be aimed for, refrained from, or continued by the subject will be printed on a lifestyle advice sheet consisting of computer-based lifestyle recommendations and a free-comment section for use by the clinical diabetes educator.The lifestyle recommendations consist of five sections. Sections I and II provide positive feedback about favorable behaviors to increase self-awareness about preventive behaviors. RD item(s) and RP item(s) identified as behavior(s) which should be continued will be indicated as follows.Section IYour current behaviors(s) shown below are effective for maintaining a favorable total energy intake. Be confident in continuing these actions.
Section IIYour current behavior(s) shown below are effective for maintaining a favorable physical activity level. Be confident in continuing these actions.

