### 2.4. Primary Outcomes

#### 2.4.1. Changes in Total Energy Intake, Fat-Energy Ratio, and Physical Activity

The primary outcomes of this study are changes in total energy intake, fat-energy ratio, and physical activity levels between baseline and the end of the intervention period. These variables will be measured by self-administered questionnaires. The questionnaires include a dietary measurement scale (Modified-Ministry of Health and Welfare-Food Questionnaire (M-MHW-FQ)) and a physical activity scale (International Physical Activity Questionnaire (IPAQ)). The M-MHW-FQ has been shown to be a reliable method of calculating energy intake and fat-energy ratio [56]. The IPAQ has been shown to be a valid method of assessing physical activity across various life activities, including during leisure activities [57–59].

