### 2.6. Data Collection

Data collected at the time of recruitment and at 1 week and 3, 6, and 12 months after recruitment will be used in this study. Background characteristics will be assessed at the time of recruitment: whether he/she has impaired glucose tolerance, abnormalities of lipid metabolism, hypertension or hyperuricemia; living status; occupational status; educational status. Baseline values for outcome measures related to lifestyle behaviors will be collected at 1 week after recruitment because participants must spent more than 15 minutes to answer the questionnaire for lifestyle assessment, and it is infeasible to order them about completing it during medical checkup. All questionnaires will be sent and returned via mail, except for the questionnaire completed at the time of recruitment. We will phone participants or mail a reminder if the questionnaire has not been returned until deadline, four weeks after each questionnaire had been sent. Biomedical data were collected at recruitment and will be collected again at 12 months.

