### 2.11. Statistical Analysis

Statistical analysis will be carried out on an intention-to-treat basis. We will summarize continuous variables using means and standard deviations, and categorical variables using counts and percentages.

The effects of GC will be investigated by comparing the GC&LI and LI groups. Similarly, the effects of LI will be investigated by comparing the LI and control groups. Primary outcomes will be analyzed by ANCOVA, adjusting for baseline values. Differences between groups in secondary outcomes at each assessment point will be analyzed by the Student's *t*-test for continuous variables or the Mann-Whitney *U* test for ordinal variables.

In all tests, a *P* value of <0.05 by two-tailed test will be considered significant. Analysis will be performed using SAS 9.2 (SAS Institute, Cary, NC, USA) software for windows.

All study protocols have been approved by the institutional review board of the School of Medicine, The University of Tokyo and Social Insurance Chuo General Hospital. Clinical Trial Registration: UMIN-CTR: UMIN00003589, UMIN00003636.

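### The primary ANCOVA names no covariate beyond the outcome's own baseline, and continuous secondary outcomes are compared by unadjusted t-test, although sex and BMI are on record from recruitment for all 216 subjects: precision is given up that costs almost nothing to keep

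*Protocol article*

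**What the plan says.** - **Primary model** (protocol article, 2.11): "Primary outcomes will be analyzed by ANCOVA, adjusting for baseline values". No further covariate is named. The outcomes are changes in energy intake, fat-energy ratio and physical activity (2.4.1).
- **Contrasts** (2.11): "The effects of GC will be investigated by comparing the GC&LI and LI groups". The LI effect is taken from LI against control.
- **Secondary outcomes** (2.11): group differences at each assessment point, by Student's t-test if continuous and Mann-Whitney if ordinal. No baseline or other adjustment is given.
- **When the lifestyle baseline is taken** (2.6): "Baseline values for outcome measures related to lifestyle behaviors will be collected at 1 week after recruitment". Section 2.1 instead has "Data collected at preintervention, immediately post-GC (baseline), and at 1 week and 3, 6, and 12 months post-GC will be analyzed". Section 2.3.1 places counseling right after consent: "After written consent was obtained, subjects underwent genetic counseling with a certified genetic counselor". On either timing, the lifestyle baseline in GC&LI follows counseling.
- **What is known at recruitment** (2.6, Table 4): biomedical data, including BMI, are collected then. Table 4 gives sex, weight and BMI for 75, 70 and 71 subjects; only the three lifestyle variables carry the reduced counts of 69, 63 and 57.
- **Role of sex elsewhere** (2.3.2): in the advice software, "subjects will be divided into four groups according to their combination of risk factors, sex, and physical activity level". The Discussion lists sex among the common variables in diabetes risk models, and the Background quotes different mean BMI for Japanese men and women.

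**The concern.** Sex is likely to predict energy intake and activity. It is complete, and no intervention can alter it. The one covariate that the model does name is, in the GC contrast, measured after counseling and absent for some subjects. Using only that covariate leaves unused the information that is complete and certainly unaffected by treatment.

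Two things are at stake. The first is precision in both contrasts. The second is that GC&LI happens to have fewer men than LI, so for this particular allocation its expected intake would be somewhat lower with no GC effect at all. For secondary outcomes such as BMI the case is simpler: a recruitment baseline exists and the named test does not use it.

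**Working it through.** **The plan's own figure.** A two-sample t-test for 0.5 SD, 80% power and two-sided 5% needs 63.77, so 64 per arm; 64/0.9 = 71.1, so 72. The stated sample size reproduces and is not affected by this point.

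**Sex imbalance (Table 4).** GC&LI 40/75 = 53.3%; LI 47/70 = 67.1%; difference d = 0.138. Pearson p = 0.090, Fisher p = 0.13. LI against control: 67.1% - 63.4% = 3.8 points before rounding.

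**Missing lifestyle baseline (Results, Table 4 footnote).** GC&LI 6/75 = 8.0%, LI 7/70 = 10.0%, control 14/71 = 19.7%. GC contrast 13/145 = 9.0%; LI contrast 21/141 = 14.9%; three arms 27/216 = 12.5%.

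**What omitting sex costs for energy intake**

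Inputs from the article:
- overall SD 420.8, with male share p = 132/216 = 0.611
- alternatively, the pooled SD of the two GC-contrast arms, √[(68×415.3² + 62×335.5²)/130] = 379.3, with p = 87/145 = 0.60
- observed baseline gap, GC&LI minus LI: 1782.8 - 1689.9 = 92.9 kcal/day

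Assumptions, because the article gives neither figure:
- male-female difference D of 200-400 kcal/day
- within-sex baseline to follow-up correlation r of 0.4-0.6

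Formulas:
- variance between sexes S = p(1-p)D²; variance within sex W = SD² - S
- slope in the baseline-only ANCOVA b = (rW + S)/SD²
- shift (i), if baseline intake differs between arms only as the sex split implies: (1-b)·D·d
- shift (ii), given the observed +92.9 gap: (1-r)·D·d + (b-r)·92.9
- share of residual variance that sex removes: 1 - W(1-r²)/[SD²(1-b²)]

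Both shifts lower GC&LI relative to LI, so they favor GC.

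| SD | D | r | b | shift (i) | shift (ii) | variance removed |
|---|---|---|---|---|---|---|
| 420.8 | 200 | 0.6 | 0.621 | 10.5 | 13.0 | 1.3% |
| 420.8 | 200 | 0.4 | 0.432 | 15.7 | 19.6 | 2.2% |
| 420.8 | 400 | 0.6 | 0.686 | 17.4 | 30.1 | 5.1% |
| 420.8 | 400 | 0.4 | 0.529 | 26.0 | 45.1 | 8.4% |
| 379.3 | 200 | 0.6 | 0.627 | 10.3 | 13.5 | 1.6% |
| 379.3 | 200 | 0.4 | 0.440 | 15.5 | 20.3 | 2.8% |
| 379.3 | 400 | 0.6 | 0.707 | 16.2 | 32.0 | 6.3% |
| 379.3 | 400 | 0.4 | 0.560 | 24.3 | 48.0 | 10.3% |

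Worked last row: SD² = 143,868; S = 0.24×160,000 = 38,400; W = 105,468; b = (42,187 + 38,400)/143,868 = 0.560. Shift (i) = 0.440×55.2 = 24.3. Shift (ii) = 0.6×55.2 + 0.160×92.9 = 33.1 + 14.9 = 48.0.

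As a share of the 0.5 SD design effect, each shift set against half of its own SD, the range is 5% to 25%. With 69 against 63 subjects, the probability of a significant GC result under no GC effect, *conditional on this allocation*, is 5.4-7.3% for shift (i) and 5.6-14.0% for shift (ii).

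**A secondary outcome, using figures in the article.** The Background gives mean BMI 23.5 for Japanese men and 21.4 for women, a gap of 2.1. Then 2.1×0.138 = 0.29 kg/m², and 0.29/3.0 = 0.10 SD (overall SD from Results). This applies if the t-test is run on 12-month levels. Section 2.5.2 is titled as changes, so if change scores are tested the carry-over is smaller, but the baseline is still not used as a covariate.

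**The case against.** **The method is valid as it stands.** Allocation was random and baseline-adjusted ANCOVA is a standard analysis. The sex split is within chance, and averaged over possible allocations the type I error stays at 5%. This is correct. A reader might infer that the late or incomplete lifestyle baseline leaves a sex bias in the GC contrast. The article does not support that: baseline timing and missing questionnaires do not create a sex imbalance, and a sex term does not cure either of them.

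**The size is easily overstated.** With no baseline adjustment at all, the same assumed 200-400 kcal difference gives a shift of 28-55 kcal/day and conditional rejection of 6.6-11.4% at 64 per arm. That describes a model nobody plans. The relevant figures are those above, with baseline in the model. The 12.5% missing is likewise the three-arm total; the GC contrast loses 9.0%, almost equally in both arms.

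**GC&LI has the higher baseline intake despite fewer men.** This is a fair observation, but it does not cancel the shift. The baseline-only slope b also carries the sex difference and so exceeds the within-sex slope r. Applied to a gap that runs against the sex split, it over-corrects in favor of GC, which is why shift (ii) exceeds shift (i).

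**Limits that stand.** The sex difference is assumed, and the sex split among the 132 subjects with a lifestyle baseline in the GC contrast is not reported. The software's use of sex is weak support, because the primary outcomes come from other instruments. Choosing sex because Table 4 looks uneven would be data-driven, so the grounds must be prognostic. Further covariates may also sit in a fuller plan that is not shown; the article does not say that baseline is the only one.

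**Conclusion.** This is a specific and nearly free improvement, not the correction of an invalid analysis. The article states a primary model with one named covariate and unadjusted tests for continuous secondary outcomes, while prognostic variables recorded before counseling could act are complete for all randomized subjects. For energy intake, leaving out sex gives up about 1-10% of residual variance. Given this allocation, it leaves about 10-48 kcal/day in favor of GC in GC&LI against LI. Both ranges rest on the assumed sex difference of 200-400 kcal/day and within-sex correlation of 0.4-0.6; the upper end of the shift also takes the observed 93 kcal baseline gap as given. No comparable figure can be derived for fat-energy ratio or physical activity.

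The post-counseling lifestyle baseline, the disagreement between 2.1 and 2.6 about when it is taken, and its missing values (9.0% in the GC contrast, 14.9% in LI against control) are separate issues.

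**What to change.** Before outcome data are seen, amend section 2.11 to:

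1. Name sex and recruitment BMI (or weight) as covariates alongside the baseline value in the ANCOVA for all three primary outcomes and both contrasts, with the reason given as expected prognostic value and not the observed imbalance.
2. Analyze continuous secondary outcomes by ANCOVA with their recruitment baseline where one was collected, plus the same covariates. Where BMI or weight is itself the outcome, its recruitment value is the baseline, so only sex is added.

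The cost is a short amendment and a few degrees of freedom, with no new data. The article describes the trial as ongoing, its analyses as still to come and the analyst as blinded to allocation (2.9), so the change can still be prespecified.

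Dropping the lifestyle baseline from the GC contrast in favor of sex and BMI alone is not proposed here. At the assumed correlations that baseline explains 16-36% of within-sex variance (0.4² to 0.6²), so removing it is a debatable trade-off that belongs with the separate question of its timing.

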## 1. Background

The number of patients with type 2 diabetes has rapidly and continuously increased in recent years and has become a global burden. Development and implementation of strategies to prevent type 2 diabetes are therefore urgently required. Identification of a high-risk population is one of the most important steps in the development of effective and efficient prevention strategies. Several risk factors for type 2 diabetes have been identified in epidemiological studies. Obesity is the most common risk factor for type 2 diabetes, and a vast amount of literature has reported on interventions aiming to reduce obesity.

 The effectiveness of lifestyle intervention for diabetes prevention has been confirmed by large, randomized, controlled trials in both Western countries [1–3] and Asian countries [4–7]. The subjects of these studies were at high risk for developing diabetes, being obese, and/or having impaired glucose tolerance. The goal of lifestyle interventions in these studies was mainly weight reduction. All of these studies definitely succeeded in preventing diabetes, while weight reduction patterns differed between Asian and Western countries. Studies in Asian countries showed a preventive effect with a smaller weight reduction (0 to 2.5 kg/year) [6, 7] than those in Western countries (4.2 to 7.0 kg/year) [2, 3]. These results reflect obvious differences in baseline body mass index (BMI) among different regions. The target population in preventive research trials usually has a BMI of ≥30 kg/m^2^ in Western countries and about 25 kg/m^2^ in Asian countries [8]. Recent global epidemiological meta-analysis has shown that BMI is strikingly lower in Asian populations compared with Oceania, Australasia, Europe, and North America [9]. Among developed countries, Japanese males have the lowest mean male BMI (23.5 kg/m^2^) and Japanese females have nearly the lowest mean female BMI (21.4 kg/m^2^) [9]. Moreover, Japanese patients with diabetes characteristically have a relatively low BMI [10]. Focusing on obesity would therefore be a less efficient method of identifying high-risk individuals in Asian countries than in Western countries, and it is necessary to focus on risk factors other than obesity.

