#### 2.5.2. Changes in Biomedical Characteristics

 Biomedical data collected from hospital records at baseline and at 12 months (age, BMI, waist circumference, and levels of HbA_1C_, fasting blood glucose, triglyceride, LDL cholesterol, and HDL cholesterol) will be used in the analyses.

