#### 2.5.3. Change in Risk Perception and Recognition About Diabetes, and Attitude towards Its Prevention

Subjects' perception and recognition about diabetes and attitude towards its prevention will be assessed before GC session (baseline for these variables) and 1 week after the session in order to evaluate the effect of GC on subjective aspect.

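### Secondary outcomes get unadjusted tests although pre-intervention baselines exist for the biomedical measures and risk perception, and the text does not settle whether change or follow-up value is tested

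*Protocol article*

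**What the plan says.** Section 2.11 names two methods. For the primary outcomes: "Primary outcomes will be analyzed by ANCOVA, adjusting for baseline values". For the others: "Differences between groups in secondary outcomes at each assessment point will be analyzed by the" Student's t-test if continuous, with Mann-Whitney U for ordinal variables and no covariate. The contrasts are GC&LI versus LI for counseling and, for the lifestyle intervention, "Similarly, the effects of LI will be investigated by comparing the LI and control groups". The criterion is a P "value of <0.05 by two-tailed test will be considered significant".

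The secondary outcomes have different baselines:

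- **Biomedical measures (section 2.5.2, headed as changes):** "Biomedical data collected from hospital records at baseline and at 12 months". Section 2.6 places the first collection at recruitment.
- **Risk perception, recognition and attitude (section 2.5.3, headed as change):** assessed "before GC session (baseline for these variables) and 1 week after the session".
- **Lifestyle behaviors (sections 2.5.1 and 2.6):** the baseline questionnaire comes one week after recruitment. By then the GC&LI group has had its counseling.

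**The concern.** Section 2.11 and the headings of 2.5.2 and 2.5.3 do not clearly describe the same quantity. Read literally, section 2.11 compares groups at an assessment point, which for the biomedical measures means the 12-month value. The headings speak of change from baseline. The two readings can differ greatly in precision.

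The biomedical measures come from hospital records. They are the only outcomes that do not rest on the answers of participants who, by section 2.9, know their group, so they are the natural check on the self-reported primary result. On the literal reading that check is weaker than the data allow, and it includes whatever imbalance randomisation left at baseline. Table 4 shows mean BMI of 22.1, 22.5 and 22.9 kg/m² in GC&LI, LI and control.

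**Working it through.** **The plan's own figure.** For 0.5 SD, 80% power and two-sided 5%, the noncentral t calculation gives 63.8, so 64 per arm. Then 64/0.9 = 71.1, so 72. Section 2.7 reproduces and is not in question.

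**Inputs for BMI, LI versus control (Table 4).** LI: 22.5 ± 2.7, n = 70. Control: 22.9 ± 3.3, n = 71.

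- Pooled SD = √[(69 × 2.7² + 70 × 3.3²)/139] = 3.02.
- SE of an unadjusted difference = 3.02 × √(1/70 + 1/71) = 0.51 kg/m².
- Difference detectable with 80% power (noncentral t) ≈ 1.43 kg/m².

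**Reference effect.** The Background cites for Asian trials a "smaller weight reduction (0 to 2.5 kg/year"). Mean weight over the three arms is (75 × 60 + 70 × 62.2 + 71 × 63.1)/216 = 61.7 kg, and mean BMI is 22.5. This implies a squared height of 61.7/22.5 = 2.74 m². So 2.5 kg is 2.5/2.74 = 0.91 kg/m², and 1.43 kg/m² is about 3.9 kg.

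**Relative variance.** Let r be the correlation between baseline and 12-month BMI. The document does not give r, so it is an assumption. With equal SD at both times, the variance relative to a t-test on follow-up values is 2(1 − r) for a t-test on change and 1 − r² for ANCOVA.

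| r (assumed) | Relative variance, change | Relative variance, ANCOVA | Power for 0.91, follow-up value | Power, change | Power, ANCOVA |
|---|---|---|---|---|---|
| 0.5 | 1.00 | 0.75 | 43% | 43% | 54% |
| 0.7 | 0.60 | 0.51 | 43% | 63% | 70% |
| 0.8 | 0.40 | 0.36 | 43% | 80% | 84% |
| 0.9 | 0.20 | 0.19 | 43% | 98% | 98% |

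The test on follow-up values discards more than half of the information only if r² > 0.5, that is r > 0.71. The variance of the change-score test relative to ANCOVA is 2(1 − r)/(1 − r²) = 2/(1 + r): 1.33 at r = 0.5, 1.18 at 0.7 and 1.05 at 0.9.

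**Observed imbalance.** LI minus control at baseline is −0.4 kg/m², or 0.4/3.02 = 0.13 SD (p = 0.43). Given that gap, the expected shift in an estimate based on follow-up values is r × (−0.4): −0.28 at r = 0.7 and −0.36 at r = 0.9. The ANCOVA standard errors at those r are 0.36 and 0.22.

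**Validity.** In 20,000 simulated trials with no effect, the unadjusted t-test rejected in 4.99%.

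**Lifestyle-behavior baseline (section 3).** It was completed by 69 of 75, 63 of 70 and 57 of 71 subjects, 189 of 216 in all. It is missing for 7 LI and 14 control subjects.

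**The case against.** A reader might infer that the plan confounds baseline differences with treatment effect. The documents do not support that. Allocation is random (section 2.8), the unadjusted test is unbiased over randomisations and keeps its level, and a gap of 0.13 SD is ordinary chance imbalance. The unadjusted SE of 0.51 already allows for gaps of this size, so it does not follow that the gap would be declared an effect. The shift is conditional on the imbalance seen, and the main cost is precision.

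A reader might also infer that most of the precision is certainly lost. That needs two things the article does not settle: that the test is on 12-month values, and that r is above 0.71. The headings of 2.5.2 and 2.5.3 allow a test on change, which at r = 0.9 has about the same power as ANCOVA. Nor do the documents support extending the BMI figures to waist, HbA1c, glucose or lipids, since no correlation is given for any of them.

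The reference effect is also generous. It is the top of the cited range and comes from trials in subjects who were obese and/or had impaired glucose tolerance, whereas this sample is nonobese. At half of it (1.25 kg, 0.46 kg/m²) ANCOVA at r = 0.9 has only about 53% power, against about 15% for the follow-up value. Applying the planned 10% dropout (63 and 64 analysed) lowers power for 0.91 kg/m² to about 39% unadjusted and 66%, 80% and 97% with ANCOVA. The contrast remains.

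A condensed article may leave detail to a fuller plan. Here, though, section 2.11 names the test, so the choice is stated and not merely omitted. That part of the concern stands.

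**Conclusion.** The point holds as one of efficiency and clarity, not of validity. Section 2.11 specifies unadjusted tests for secondary outcomes, two of which have pre-intervention baselines and are named as changes. If the test is on 12-month values, power for a BMI difference of 0.91 kg/m² between LI and control is about 43%, where ANCOVA would give about 70% to 98% for assumed r of 0.7 to 0.9. The observed baseline gap would move the estimate by −0.28 to −0.36 kg/m² over the same range. If the test is on change, the loss against ANCOVA is about 5% in variance at r = 0.9 but 18% at r = 0.7 and 33% at r = 0.5. These figures rest on the assumed r, equal SDs at both times, and 70 and 71 subjects analysed. The primary analysis, already by ANCOVA, and the sample size are unaffected. The change is worth making, but the trial's main conclusion does not depend on it.

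**What to change.** 1. Reconcile section 2.11 with 2.5.2 and 2.5.3: state for each secondary outcome whether the follow-up value or the change is analysed.
2. Analyse continuous secondary outcomes that have a pre-intervention baseline by ANCOVA on that baseline, as for the primary outcomes. This covers the biomedical measures, and risk perception where it is continuous.
3. Do not adjust GC&LI versus LI for the one-week lifestyle-behavior baseline. It is taken after counseling, and adjusting for it could remove part of the counseling effect. For LI versus control the adjustment is optional. If it is used, say how the missing baselines (7 of 70 LI, 14 of 71 control) are handled.

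**Cost.** Items 1 and 2 take a sentence or two in section 2.11 and no new data: Table 4 reports the biomedical baselines it lists on all 75, 70 and 71 subjects. Item 3, if the optional adjustment is chosen, also needs a rule for the missing baselines.
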